## Abstract

**Objective:** It is unclear whether and to what extent COVID-19 infection poses health risks and a chronic impairment of performance in athletes. Identification of individual health risk is an important decision-making basis for managing the pandemic risk of infection with SARS-CoV-2 in sports and return to play (RTP).

**Methods:** This study aims 1) to analyze the longitudinal rate of seroprevalence of SARS-CoV-2 in German athletes, 2) to assess health-related consequences in athletes infected with SARS-CoV-2, and 3) to reveal effects of the COVID-19 pandemic in general and of a cleared SARS-CoV-2 infection on exercise performance. CoSmo-S is a prospective observational multicenter study establishing two cohorts: 1) athletes diagnosed positive for COVID-19 (cohort 1) and 2) federal squad athletes who perform their annual sports medical preparticipation screening (cohort 2). Comprehensive diagnostics including physical examination, laboratory blood analyses and blood biobanking, resting and exercise electrocardiogram (ECG), echocardiography, spirometry and exercise testing added by questionnaires are conducted at baseline and follow-up.

**Results and Conclusion:** We expect that the results obtained, will allow us to formulate recommendations regarding RTP on a more evidence-based level.

## Introduction

The current coronavirus pandemic is already one of the biggest global crises and poses an extreme challenge not only for the healthcare systems but is also a real test for social solidarity. Although the infection with severe acute respiratory syndrome coronavirus 2 (SARS-CoV-2) leads in the majority of the cases to light, moderate or even no symptoms it can also have severe to fatal consequences. Current knowledge of this disease shows that not only the lungs but also the cardiovascular system, the skeletal muscle, the central as well as the peripheral nervous system, the blood and the immune system, the liver, the kidneys and further body functions might be affected [1–6].

According to current knowledge, athletes are not a risk group predisposed for a severe course of COVID-19 disease. However, this fact does not prevent athletes from infection with SARS-CoV-2 that could be associated with moderate or even stronger acute symptoms [7]. In this context, more severe courses have been described in, prior to infection, fit and healthy athletes. Myocardial involvement in terms of myocarditis, as described as a possible cardiovascular sequela in COVID-19 [2], requires special attention in athletes not only with respect to return into competitive sport (return to play, RTP). In a small case sample of 26 US college athletes, who were tested positive for SARS-CoV-2 and presented with none or only mild symptoms, four males met criteria for myocarditis in cardiac magnetic resonance imaging (cMRI) [8]. In addition, a study including 789 North American professional athletes, who were tested positive for SARS-CoV-2, reported abnormal findings in 30 cases during the cardiac screening, whereas five of these were diagnosed with inflammatory heart disease (myocarditis or pericarditis) by additionally performed cMRI [9]. In a group of 90 young adult competitive athletes, cardiac consequences of SARS-CoV-2 has been described in 3.3% of the cases with one athlete with myopericarditis and two cases with pericarditis [10]. In a larger cohort of collegiate athletes, the prevalence of clinical myocarditis as assessed on a symptom-based diagnostic algorithm was 0.3%. In the same cohort, additional MRI revealed that 2.3% of the athletes met criteria for clinical and subclinical myocarditis [11]. Additional data showed a slightly lower prevalence (1.5%) in young competitive athletes after COVID-19 as detected by primary cMRI [12]. However, the true prevalence as well as the clinical relevance of these findings are not completely clear at present [13].

In a meta-analysis, exercise-induced dyspnea has been described as one of the leading symptoms, persisting longer than 2 weeks after COVID-19 diagnosis [14]. Initial data in the actual pandemic reveal a relevant percentage of COVID-19 patients with persisting respiratory symptoms and an impairment of pulmonary function longer than 100 days after initial diagnosis [15]. With respect to athletic performance, it must be taken into account that even minor restrictive changes might limit maximum ventilation and/or disrupt respiratory economy. In addition, a disturbance of gas exchange as a result of a diffusion disturbance is likely to restrict exercise tolerance and performance. Furthermore, there is preliminary evidence of a compromised oxygen transport to the consuming tissues, which occurs at the erythrocyte level [16].

In addition to cardiac, pulmonary and other sequelae, COVID-19 has been shown to be at risk for persistent symptoms and delayed recovery, actually termed as “long-COVID-syndrome” [17]. A meta-analysis, which assessed more than 50 long-term effects extending the acute phase of COVID-19 showed that 80% of COVID-19 patients suffered from at least one symptom persisting more than 2 weeks after initial diagnosis [14]. Persisting symptoms with highest frequencies were fatigue (58%), headache (44%), attention disorder (27%), hair loss (25%) and dyspnoea (24%). It is assumed that at least 10% of the COVID-19 survivors develop a long-COVID-syndrome, which may underestimate the real prevalence [18]. To date it remains speculative, how many of the athletes are affected and to what extent “long-COVID-syndrome” is present in physical active subjects and in particular competitive athletes, exhibiting only mild or no symptoms during the acute phase of the infection.

The complex and at this time point incompletely understood clinical picture of COVID-19 disease leads to the question of how reintegration into sport can be achieved with an acceptable risk after overcoming the acute phase of the COVID-19 infection [19]. For this purpose, a number of recommendations have been published [2, 20–22], which summarize primarily expert consensus statements. Thus, for the development of more evidence-based RTP concepts there is a need for extensive research in this field [23]. Because of the current uncertainty of long-term course of COVID-19 disease, the same is true with respect to the necessity of long-term follow-ups in affected athletes [24].

From today’s perspective, it is unclear whether and to what extent a mild or even asymptomatic COVID-19 infection poses an acute health risk and a more chronic impairment of athletic performance in competitive athletes. The identification and envisaged quantification of such impairments are an important decision-making basis for the management of the pandemic risk of this infection in sports and for athletes’ reintegration and return into competitive sports. In this context, it is important to note that even a slight decrease in physical performance, not perceivable in daily living, may compromise competitive success in elite athletes. Nevertheless, to delineate subtle perturbations of COVID-19 disease on exercise performance and its underlying pathophysiology may also have importance for the non-athletic population. With respect to the prevalence of COVID-19 in competitive athletes, reliable epidemiological data is still lacking. Since asymptomatic or oligosymptomatic courses are presumably common in younger people [12], a high number of unreported cases of passed infections has to be expected, also and maybe particularly among competitive athletes. Nevertheless, it is unclear whether the prevalence of COVID-19 infection in competitive athletes differs from that of the general population in the same age-group. Moreover, it is unclear, whether there may be differences within the athlete population, depending on the type of sports and performance level, the grade of intensive physical contacts and the extent of sports-related travel activities. As described, the COVID-19 pandemic represents one of the greatest challenges also for competitive sports and, in particular, its sports medicine monitoring. In our opinion, this challenge can only be addressed in a multicentric approach. The objectives of our project are to investigate open questions about the type and frequency of potential health risks and remaining symptoms, to assess consequences of this disease on athletic performance and to determine the seroprevalence of COVID-19 diseases in the athletic population. In this context, close networking of the sports medicine centers in Germany is also useful against the background that although the infection rates exhibit intermediate drops and vaccination rates increase, the occurrence of virus mutations [25] and an unclear duration of immunity after vaccination clearly reflect that the pandemic is still in progress.

## Methods

### Central Research Questions

This study aims 1) to analyze the longitudinal rate of seroprevalence of SARS-CoV-2 in national squad athletes, 2) to assess acute and prolonged health-related consequences in athletes infected with SARS-CoV-2, and 3) to reveal effects of the COVID-19 pandemic in general and of a cleared SARS-CoV-2 infection on physical performance.

### Design and Setting of the Study

CoSmo-S (COVID-19 in elite sports—A multi-center cohort study) is organized as a prospective observational multicenter hybrid cohort study by establishing and investigate two study cohorts: 1) Athletes diagnosed positive for Covid-19 disease (cohort 1, C1) and 2) federal squad athletes and Paralympic athletes* who routinely present themselves for their annual sports medical preparticipation screening (cohort 2, C2) (Figure 1).

**FIGURE 1 F1:**
[figure not shown]
Prospective multicenter cohort study flow diagram of cohort 1 and cohort 2 (COVID-19 in German competitive sports: Protocol for a prospective multicenter cohort study; Germany, 2020).

Examinations are performed in 13 sports medical outpatient clinics in Germany, licensed from the German Olympic Association (DOSB) for preparticipation screenings in federal squad athletes and Paralympic athletes. Most of the outpatient clinics are located at universities. In both cohorts the athletes receive comprehensive diagnostics at baseline (*t*
_0_), as well as follow-up (C1: +1 year, C2: +1 and +2 years), including medical history, physical examination, laboratory blood parameters, resting and exercise ECG, echocardiography, spirometry and exercise testing added by questionnaires for anamnesis and on COVID-19—specific aspects such as type and duration of symptoms (additionally +6 and +18 months), respectively. Biobanking is performed on plasma and serum samples as well as optionally on isolated peripheral blood mononuclear cells (PBMC) for further analyses (for details see Tables 1, 2).

**TABLE 1 T1:** Schedule of diagnostic data collection in Cohort 1 and Cohort 2 in the prospective multicenter cohort study (COVID-19 in German competitive sports: Protocol for a prospective multicenter cohort study; Germany, 2020).

	Cohort 1				Cohort 2				
Time point	*t* _0_	*t* _1_	*t* _2_	*t* _3_	*t* _0_	*t* _1_	*t* _2_	*t* _3_	*t* _4_
Month	0	6	12	18	0	6	12	18	24
Assessments									
Screening and study inclusion	X				X				
Questionnaires									
COVID-19 specific questionnaire									
- Prior/intermediate SARS-CoV-2 testing	X	X	X	X	X	X	X	X	X
- Contact situations with SARS-CoV-2 positive subjects	X	X	X	X	X	X	X	X	X
- Prior/intermediate acute symptoms of infection	X	X	X	X	X	X	X	X	X
- Experience of unusual/chronic symptoms	X	X	X	X	X	X	X	X	X
- Necessity and duration of quarantine	X	X	X	X	X	X	X	X	X
- SARCS-CoV-2 vaccination state	X	X	X	X	X	X	X	X	X
- Actual exercise tolerance and performance	X	X	X	X	X	X	X	X	X
Anamnesis									
- Medical history	X		X		X		X		X
- Training report	X	X	X		X	X	X	X	X
- Family history	X		X		X		X		X
- Medication	X		X		X		X		X
- Dietary habits/dietary supplements	X		X		X		X		X
Medical examination									
Anthropometry									
- Height, weight, body mass index	X		X		X		X		X
- Percent body fat	X		X		X		X		X
Physical examination	X		X		X		X		X
Blood sampling and analyses									
Blood analyses									
- Blood cell and differential cells counts, C-reactive protein, liver enzymes, creatinine, ferritin, troponin^a^,	X		X		X		X		X
d-dimers^a^, urine protein			X		X		X		X
- SAR-CoV-2 antibody testing	X		X		X		X		X
- Biosampling (plasma and serum)	X		X		X		X		X
- Isolation of PBMC^b^ (optional)	X		X		X		X		X
Cardiorespiratory diagnostics									
Twelve-lead-resting electrocardiogram (ECG)^c^	X		X		X		X		X
Resting blood pressure	X		X		X		X		X
Resting spirometry									
- Static lung variables^d^	X		X		X		X		X
- Dynamic lung variables^e^	X		X		X		X		X
Echocardiography									
- Morphology, left and right heart dimensions^f^	X		X		X		X		X
- Left and right heart systolic and diastolic function^g^	X		X		X		X		X
- Strain analysis (optional)	X		X		X		X		X
- Doppler analysis^h^	X		X		X		X		X

a Only if individually indicated.

b PBMC, peripheral blood mononuclear cells.

c Interpretation of the ECG of athletes according to [26].

d Inspiratory vital capacity (IVC), Forced vital capacity (FVC).

e One-second vital capacity (FEV1), Tiffenau–index (FEV1/FVC), peak exspiratory flow (PEF), maximum exspiratory flow at 75% FVC (FEF75%) and 25–75% FVC (FEF25-75%).

f Left ventricular enddiastolic diameter (LV-EDD), left ventricular endsystolic diameter (LV-ESD), Right ventri-cular enddiastolic diameter (RV-EDD), mode), enddiasystolic volume (EDV), endsystolic volume (ESV) left and right atrial dimensions (planimetric and M-mode), heart volume (HV, absolute and relative). Basal right ventricular diameter (RVD1), systolic septal thickness (LV-STs), diasystolic septal thickness (LV-STd), systolic posterior wall thickness (LV-PWs), diastolic systolic posterior wall thickness (LV-PWs), LV mass (LVM), LV mass index (LVMi), signs and dimension of pericardial effusion.

g Fractional shortening (FS), ejection fraction (EF, by ESD and EDV, according Simpson), regional wall motion, tricuspid annular plane systolic excursion (TAPSE), E-wave, A-wave, E/A-ratio, E′-wave septal, E′- wave lateral and E/E′– wave ratio.

h Colour-, PW- and CW-doppler of heart valves, maximum systolic pulmonal artery pressure *via* maximum tricuspidal regurgitation velocity (maximum PAPsys).

**TABLE 2 T2:** Schedule of ergometric data collection in Cohort 1 and Cohort 2 in the prospective multicenter cohort study (COVID-19 in German competitive sports: Protocol for a prospective multicenter cohort study; Germany, 2020).

	Cohort 1				Cohort 2				
Time point	*t* _0_	*t* _1_	*t* _2_	*t* _3_	*t* _0_	*t* _1_	*t* _2_	*t* _3_	*t* _4_
Month	0	6	12	18	0	6	12	18	24
Exercise testing									
Incremental exercise test^a^									
- Twelve-lead-electrocardiogram	X		X		X		X		X
- Blood pressure	X		X		X		X		X
- Capillary blood lactate^b^	X		X		X		X		X
- Rate of perceived exertion (BORG-scale)^c^	X		X		X		X		X
- Pulse oximetry	X		X		X		X		X
- Breath gas analysis/Spiroergometry (optional)^d^	X		X		X		X		X
Additional ramp test (if possible)^e^									
- Breath gas analysis/Spiroergometry^f^	X		X						
- Capillary blood lactate (pre/post exercise)	X		X						
- Capillary blood gases	X		X						

a Treadmill, bicycle, canoe or rowing ergometry with stepwise increase of exercise load until voluntary exhaustion. The incremental exercise test is performed in both cohorts.

b Calculation of exercise load at the lactate threshold (LT), individual anaerobic threshold (IAT) and at the end of exercise from the lactate-performance curve.

c Assessment of perceived exertion (RPE) pre-exercise, at the end of every stage during the test and post-exercise according the qualities “overall,” “muscular,” and “ventilatory.”

d Additional breath gas analysis is performed in cases where breath gas analysis was also performed in an existing previous test.

e An additional ramp test with breath gas analysis is performed only in C1 provided that the athletes tolerate a second test. Protocol: bicycle ergometry, starting at an initial load of .5 W per kilogram body mass with a continuous increment of .5 W per kilogram body mass until voluntary exhaustion.

f Measures: maximum oxygen consumption (VO2max), ventilatory threshold 1 (VT1), respiratory compensation point (RCP), maximum minute ventilation (VEmax), tidal volume, oxygen pulse, ventilatory equivalents (VE/VO2 and VE/VCO2), endtidal VCO2 (ET- VCO2).

In C1, diagnostic is expanded by breath gas analysis and—if clinically indicated—by further diagnostics such as cMRI, lung computed tomography (CT) or assessment of lung diffusion capacity. Moreover, pre-existent diagnostic findings related to the actual SARS-CoV-2 infection of the individuals in C1 are documented. In C2, data from previous exercise testing and resting spirometries, mostly available from the last preparticipation screening prior to the COVID-19 pandemic, are also included. To ensure comparability of data from exercise testing, it is recommended to use the identical exercise testing protocols at the post-COVID-19 test for each subject as performed in the pre-COVID-19 examination.

After 6 months (*t*
_1_), initial diagnostics in C1 and C2 are followed by a web-based questionnaire addressing follow-up medical history and COVID-19 specific aspects. One year post-baseline, a follow-up examination (*t*
_2_) including the diagnostic procedures from *t*
_0_, is planned for each participant. In turn, web-based questionnaire is repeated at 18 months (*t*
_3_) in C1 and C2 and another examination will take place at 24 months (*t*
_4_) only in C2.

### Characteristics of the Participants

#### Inclusion Criteria

In C1 inclusion criteria comprise an age of at least 18 or older, proven infection with SARS-CoV-2 assessed by 1) positive swap (polymerase chain reaction, PCR) or 2) positive serum SARS-CoV-2 IgG plus 3) typical acute symptoms and 4) ambiguous sport activities with a minimum of three training sessions per week corresponding to a minimum energy expenditure of 20 MET hours per week. Inclusion criteria of C2 are an age of 14 years or older, being member of the German federal squad or Paralympic federal squad and presentation for annually routine preparticipation screening at one of the DOSB licensed study centers. In both cohorts, inclusion requires a written informed consent of all participants. If the participants in C2 are not aged 18 years or older, the written consent has to be additionally signed by the agreeing parents of the participant. If a participant of C2 develops COVID-19 during the course of the study and is 18 years or older, this athlete is also included in C1.

#### Exclusion Criteria

Exclusion criteria in C1 and C2 are acute COVID-19 infection with a positive SARS-CoV-2 PCR within the last 2 weeks, refusal of venous blood sampling, insufficient skills of German language, acute or chronic disease that does not allow inclusion as estimated by the study physician or withdraw of the agreement to participate in the study.

### Data Collection

A large part of the data is collected as part of routine diagnostics as recommended prior return to sports and/or to clarify persistent exercise intolerance after COVID-19 disease [20] in C1 and as defined for the preparticipation screening program of the DOSB for squad athletes [27] in C2. Study specific data collection and diagnostics include a COVID-19 specific questionnaire, SARS-CoV-2 antibody testing and biobanking of plasma and serum samples. Since the national squad athletes present themselves annually at the DOSB-licensed centers as part of the annual examinations, there are in the majority of athletes examination results from the pre-pandemic time available. These allow a more precise assessment of intra-individual comparison between pre- and post-COVID-19 examination results of the same person and to delineate possible effects of the COVID-19 pandemic on physical performance.

### Data Management

All data are primarily documented in the original patient charts of the athletes and then transferred to the electronic CRF (eCRF) of the data capture system REDCap (Research Electronic Data Capture) [28, 29] hosted at Paderborn University. REDCap data entry is implemented following the diagnostic structure outlined in Tables 1, 2 using repeatable instruments. Validation of data entry is implemented where applicable. Access to patient data and data entry is restricted to the respective study center by means of data access groups corresponding to the 13 study centers. Data transfer to and from REDCap is fully encrypted.

In the initial phase of the study, COVID-specific questionnaires are paper-based and detached in the course by a tablet—based solution, which automatically transfers the results to the REDCap data base. Tablet and web-based questionnaires are implemented utilizing REDCap’s survey function. For missing data, no assumptions are made. After enrollment into the study, the athletes were coded with an eight-digit alphanumerical code under which all entries will be made in the database and which can only be assigned at the respective study center. In order to reduce an investigator-specific bias on the interpretation of exercise test data, all raw data from exercise tests are pooled and then evaluated in a standardized manner according to identical calculation criteria.

### Quality Aspects and Monitoring

Upon initialization of the study, all study centers are briefed on the data entry by the IT-team of the study. During the initial process of the implementation, minor adjustments of the data base are done to further improve the process of data entry. An internal monitoring is implemented to ensure valid data transfer and documentation in the data capture system REDCap. Quality checks of the data are performed and allow the generation of queries. Moreover, monitoring includes randomly organized visits to single study centers to check for the validity of the data transfer to the data capture system. Missing data are labelled as N/A or N/D and, if appropriate, added by a comment.

### Statistical Analysis

For relevant categorical variables as e.g. documented symptoms experienced during the COVID-19 infection, persistent symptoms, presence/absence of antibodies or quarantine measures absolute and relative frequencies will be presented. To investigate associations of infection characteristics, patient characteristics or sports-related characteristics on prolonged recovery after COVID-19 infection and delayed return to sports odds ratio will be calculated and Chi-square tests will be performed trying to identify potential risk factors for COVID-19 infection, long absence from training and competition, and long-lasting or severe symptoms. For continuous outcomes, means and standard deviations or medians and interquartile ranges will be calculated. Multivariable regression models will be fitted to the data to consider multiple independent variables simultaneously and to account for potential confounders. All statistical tests will be performed two-sided on a significance level of *α* = 5%. For relevant measures 95% confidence intervals will be estimated.

In both cohorts, sample size was not formally calculated. In C1, recruitment numbers depend on the development of the pandemic, but we estimate a minimum of 1,000 athletes, who will be included into C1. In C2, reaching the proposed minimum number of 2,500 federal squad athletes and Paralympic athletes means, that at least 62% of all German squad athletes will be included in CoSmo-S. Actually, we have defined no upper limit for athlete´s recruitment in C1 and C2.

### Machine Learning-Based Outcome Predictions

Clinical predictive models rely on machine or deep learning (ML/DL) methods. Unlike their more traditional application on retrospective data (such as electronic health records and billing data), prospectively collected data such as in this project have comparatively low percentages of missing and erroneous values, increasing the predictive performance without data imputation. Clinically significant outcome variables such as the physical performance or other health-related consequences will be binarized and serve as target variables, while the other data will become feature variables. The actual models can either be time-insensitive (e.g., traditional ML models, such as XGBoost or Random Forest) or consider the longitudinality of the observations (e.g., deep learning architectures, such as long short-term memory (LSTM) networks). The input data will be split into training, validation, and test sets. All modeling results will undergo a feature importance analysis to assess the impact of individual features on the prediction performance.

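### The machine-learning plan dichotomises physical performance without need, and its feature rule does not exclude data measured with, after or as part of the target

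*Protocol article*

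**What the plan says.** Two rules stand in the section Machine Learning-Based Outcome Predictions, in one sentence: outcomes such as physical performance "will be binarized and serve as target variables, while the other data will become feature variables".

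- On the target, no cut-point is given.
- On the features, no limit is set by time of measurement or by relation to the target.

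The same section allows time-insensitive models (XGBoost and Random Forest are the examples) or models that "consider the longitudinality of the observations", such as LSTM networks. It plans a feature importance analysis for all of them. On partitioning it says only: "The input data will be split into training, validation, and test sets".

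Three other places matter:

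- The Introduction argues that in elite athletes even a small loss of performance, too small to notice in daily life, can cost competitive success.
- The footnotes to Table 2 derive the loads at the lactate threshold (LT), at the individual anaerobic threshold (IAT) and at the end of exercise from one lactate-performance curve. They also list VO2max, VT1, RCP and VEmax as results of one ramp test in cohort 1 (C1).
- Results and Discussion hopes to find predictors of an individual athlete's risk of a later drop in physical function or of prolonged fatigue.

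**The concern.** A yes/no target treats all athletes on the same side of the cut as alike. An athlete who loses a little performance without crossing the cut counts as unaffected, yet this is the kind of change the Introduction wants to detect. The information is lost at any cut-point, so a cut-point fixed in a fuller plan would not recover it.

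The feature rule raises a different problem. A risk prediction uses what is known before the outcome. If every variable other than the target may be a feature, the model may use results from the same test, or from later visits, that largely restate the target. Such variables would dominate both the accuracy measure and the feature importance ranking. The analysis would then show that performance measures agree with one another, not which athletes are at risk.

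**Working it through.** The article gives no cut-point, expected AUC or split ratio for this analysis, so there is no stated figure to reproduce. The calculations below are illustrations on assumed inputs.

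**1. Information kept after dichotomising.** Assume a normally distributed outcome cut at the quantile p. The asymptotic efficiency relative to the continuous outcome is φ(z_p)² / [p(1 − p)], where φ is the standard normal density.

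| Cut (share below) | z_p | φ(z_p) | Efficiency | 1,000 athletes carry the information of |
|---|---|---|---|---|
| 50% | 0 | 0.399 | 0.159 / 0.25 = 0.64 | 637 |
| 25% | −0.674 | 0.318 | 0.101 / 0.1875 = 0.54 | 539 |
| 20% | −0.842 | 0.280 | 0.078 / 0.16 = 0.49 | 490 |
| 10% | −1.282 | 0.175 | 0.031 / 0.09 = 0.34 | 342 |

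The 1,000 is the minimum that the Statistical Analysis section expects for C1.

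**2. Is the loss forced by the method?** No. XGBoost, Random Forest and LSTM networks can all be fitted to a continuous target.

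**3. What a same-visit feature can do.** Let the target be Y, standard normal, with the event defined as the lowest 20%. Let one feature from the same visit be X = rY + √(1 − r²)·e, with e independent standard normal. The AUC of X for the event, by simulation with 200,000 draws, is:

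| r | AUC |
|---|---|
| 0.50 | 0.75 |
| 0.70 | 0.85 |
| 0.90 | 0.95 |
| 0.95 | 0.975 |

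Nothing in this set-up comes before the outcome, so none of the AUC is prediction forward in time. The documents give no correlations, so r is assumed. High values are plausible for load at IAT against load at the end of exercise, because both are read from the same curve.

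**4. Rule against purpose.** The feature rule admits load at IAT or VO2max when peak load at that visit is the target. The purpose stated in Results and Discussion is the individual risk of developing a drop. A model built as the rule is worded could score well in step 3's sense and leave that purpose unmet.

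**The case against.** Several points can fairly be made for the plan.

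- **Binarising is confined to this section.** The Statistical Analysis section summarises continuous outcomes as continuous and plans multivariable regression, and no primary inference depends on the machine-learning models. This limits the damage but does not repair the prediction models.
- **The efficiencies are asymptotic and assume normality.** They are not losses in classifier accuracy. This is correct, and they should be read only as an indication of scale. For outcomes that are naturally yes/no, binarising costs nothing; the point is about physical performance.
- **A sensible analyst would not apply the feature rule literally.** Perhaps so, and a fuller plan may restrict it. But the article states a rule here; it is not merely silent, and the rule as worded is too wide.
- **The hopes for return-to-play advice concern the whole study.** This is right. The article does not tie those recommendations to the machine-learning models alone.
- **Pre-pandemic values are less often available in C1, and limiting features to baseline would disable the longitudinal models.** Both are true, and the change below allows for them.

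A reader might go further and infer that the plan splits records without regard to athlete, so that its predictions will be inflated. The ingredients are there: C1 athletes have two examinations and cohort 2 (C2) athletes three, data are entered "using repeatable instruments", and for an adult C2 athlete who develops COVID-19, "this athlete is also included in C1". If records were split at random with 60% to 80% in training, the chance that a test record has a same-athlete record in training is 1 − (1 − t)^(m − 1) for training share t and m visits. That gives 60% to 80% with two visits and 84% to 96% with three. But the article names no split unit, a condensed article may leave it to the full plan, and the Data Management section gives each athlete one code for all entries, so grouping by athlete is possible. The documents do not support the inference.

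**Conclusion.** The point holds for the two stated rules. Dichotomising performance is unnecessary and, for a normal outcome, leaves about 64% of the information at a median cut and 34% at a 10% cut. It also sits badly with the Introduction's emphasis on small decreases. The feature rule, read literally, admits same-visit and later restatements of the target; under assumed correlations of 0.7 and 0.9, one such feature alone reaches an AUC of about 0.85 or 0.95. Discrimination and feature importance obtained that way would not speak to individual risk.

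Leakage between training and test sets is not shown. Silence on the split unit is not an error, and that matter is only a safeguard to confirm. The analysis is exploratory, so the point is worth correcting but does not threaten the study's main descriptive and regression results.

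**What to change.** 1. Model physical performance as a continuous outcome, using the pre-pandemic value where it is available. Keep any binary version secondary, at a cut-point fixed and justified in advance.
2. Restrict features to data obtained before the outcome being predicted. Earlier visits remain usable, so the longitudinal models are not lost. Exclude components of the target and quantities derived from the same test.
3. As a safeguard, confirm that all records of one athlete, across visits and across C1 and C2, stay in one partition.

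Nested or leave-one-centre-out validation, calibration and a penalised-regression benchmark would be useful additions but are optional.

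The cost is plan wording and some analysis time. No further data collection is needed. Apparent accuracy will look less favourable, because features that restate the outcome will no longer contribute.
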